### Randomization and blinding process

An assistant researcher specially trained will be responsible only for recruiting the participants to enter the study and will give them all the information about the study, obtaining their written consent in case they agree to participate.

An assistant researcher not involved with the recruitment, intervention and assessment will generate the allocation sequence. The participants will be allocated in a group that will receive a low-calorie diet for weight loss (group I) or in another group that will receive diet + PFMT (group II). Randomization will be carried out using a computational list of random numbers and will be concealed (by means of a sealed brown envelope). Women’s data will be kept only with the assistant researcher not involved with other parts of the research process to process to protect confidentiality before, during, and after the intervention. The trial is an assessor blinded in relation to the pelvic floor muscle assessment.

The senior researcher who is not involved with the recruitment, intervention delivery, and assessment will have access to the trial data. We have planned to submit the manuscript to an open-access journal that makes all data available to readers as an appendix or under request.

Figure 1 shows the flowchart for selecting women for the randomized clinical trial, following the CONSORT.

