**Methods:**

This is a protocol for a randomized controlled trial that will include obese women reporting UI and being able to contract their pelvic floor muscles. The participants will be randomly allocated in two groups: group 1 will participate in a 12-week protocol of low-calorie diet delivered by a multi-professional team at a tertiary hospital; group II will receive the same low-calorie diet protocol during 12 weeks and will additionally participate in 6 group sessions of supervised PFMT delivered by a physiotherapist. The primary outcome of the study is self-reported UI, and severity and impact of UI on women’s quality of life will be assessed by the ICIQ-SF score. The secondary outcomes will be adherence to the protocols assessed using a home diary, pelvic floor muscle function assessed by bidigital vaginal palpation and the modified Oxford grading scale, and women’s self-perception of their PFM contraction using a questionnaire. Satisfaction with treatments will be assessed using a visual analog scale. The statistical analysis will be performed by intention to treat and multivariate analysis of mixed effects will be used to compare outcomes. The complier average causal effects (CACE) method will be used to assess adherence. There is an urgent need for a high-quality RCT to investigate if the association of a low-calorie diet and PFMT can provide a larger effect in the improvement of urinary incontinence reports in women with obesity.

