### Ethic

The study was approved by the Human Research Ethics Committee of the University of São Paulo—Hospital das Clínicas of the Ribeirão Preto Medical School (HCFMRP / USP) No. 16379919.5.0000.5440 on July 9, 2019, and registered in the Clinical Trials—NCT04159467.

Any major deviation or modification of the original protocol will be reported in the Clinical Trials website and the trial records will be continuously updated as necessary.

The risks of this research basically include the possible embarrassment of the participant in answering questions related to symptoms of urinary incontinence, intestinal and vaginal pain, and embarrassment during the physical examination (vaginal palpation), in addition to feeling some discomfort during the examination and of the possible breach of confidentiality during the research.

The benefits of this research are that the participant will receive information about the anatomy of the pelvic floor, its functions, and dysfunctions, she will learn to contract this musculature and know if she is doing it correctly, contributing to prevent and/or treat its dysfunctions, in addition to also receiving a program of training for 12 weeks (if selected for group II) to strengthen the pelvic floor muscles. If you are selected for group I, you will be invited after 12 weeks to receive the same treatment as in group II.

For ethical reasons, we did not plan to prohibit any concomitant treatment. We included in the methods section our plan to monitor any concomitant treatment for pelvic floor disorders including urinary incontinence, but we expect to have homogeneous groups in relation to these variables provided by an adequate randomization and sample size.

Figure 1 shows the CONSORT (Consolidated Standards of Reporting Trials) flowchart, enrollment schedule, interventions, and study evaluations. Figure 2 shows the checklist using the SPIRIT (Standard Protocol Items: Recommendations for Interventional Trials) used in the study.

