### Sample size calculation

The sample calculation was estimated considering a significance level of 5%, power of 20%, and difference of 4 points on the final score of the primary outcome, ICIQ-SF, between groups at the end of treatment [10]. The value of 4 points is equivalent to the minimum value for change in the questionnaire score. Thus, the sample will be composed of 22 participants.

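### Randomising 22 women does not assure similar concomitant treatment in the two arms, and the planned model leaves a chance gap in baseline ICIQ-SF in the estimate

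*Protocol article*

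**What the plan says.** All statements are from the Protocol article.

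- **Ethic.** No concomitant treatment is prohibited, for ethical reasons. Concomitant treatment for pelvic floor disorders, including incontinence, is to be monitored. The section then adds: "we expect to have homogeneous groups in relation to these variables provided by an adequate randomization and sample size".
- **Sample size calculation.** "Thus, the sample will be composed of 22 participants". The target is a "difference of 4 points on the final score of the primary outcome, ICIQ-SF, between groups at the end of treatment". No standard deviation is given.
- **Randomization and blinding process.** "Randomization will be carried out using a computational list of random numbers". A researcher outside recruitment, intervention and assessment generates the sequence, and sealed envelopes conceal it. Only the assessor is described as blinded. The article gives no allocation ratio and does not say whether the list is restricted.
- **Statistical analysis.** ICIQ-SF is analysed with a linear mixed model that has random effects for individuals and fixed effects for group, time and their interaction. No baseline covariate is named. Table 2 gives two time points, baseline and post-intervention.
- **Intervention.** Only group II has supervised sessions and phone calls. Group I is offered pelvic floor muscle training (PFMT) after data collection ends.

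**The concern.** The Ethic section uses randomisation and sample size as the reason not to worry about other incontinence treatment. That reassurance has two weaknesses.

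The first is chance. With about 11 women per arm, sizeable differences in any one factor are common. The second is timing. Randomisation acts on what exists at allocation. Women know whether they are attending PFMT sessions, and those in group I spend 12 weeks without incontinence-specific training from the trial while free to seek treatment elsewhere. No sequence, blocked or not, and no sample size makes such later treatment similar between arms.

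The same smallness affects the primary estimate. If the arms differ by chance in baseline ICIQ-SF, the planned model carries part of that gap into the estimated effect. The trial yields one estimate from 22 women, so a shift that is a noticeable share of the 4-point target makes that estimate harder to interpret.

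**Working it through.** **Inputs**
- From the article: total 22; target difference 4 points; 5% significance; two arms; ICIQ-SF at baseline and 12 weeks.
- Assumed because not stated: 1:1 ratio; two-sided test; equal SDs at both times; baseline-to-final correlation ρ from 0.3 to 0.7; 20% of women using a given concomitant treatment.

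**1. The plan's own figure.** The sample of 22 cannot be reproduced, because no SD is given and power is written as 20%. Read as a 20% type II error (80% power), the SD that makes 11 per arm sufficient can be solved for:
- Normal approximation: SD = 4 / [(1.960 + 0.842) × √(2/11)] = 3.35.
- Noncentral t: SD = 3.18.

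The t-based 3.18 is used below as an assumption.

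**2. Chance imbalance in a continuous covariate at 11:11.** The standard error of a standardised difference is √(2/11) = 0.426. Then P(|difference| ≥ 0.5 SD) = 2 × [1 − Φ(0.5/0.426)] = 0.241, or 24%.

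**3. Chance imbalance in a concomitant treatment at 11:11.** The counts in the arms are two independent Binomial(11, p) variables.

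| Assumed use p | P(counts differ by 3 or more women) |
|---|---|
| 10% | 7% |
| 20% | 17.7% |
| 30% | 24% |

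This covers only use that is unrelated to arm. Use begun because of the arm comes on top and is not a matter of chance.

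**4. What the planned model does with a baseline gap.** With two time points and a free group effect, the interaction equals the difference between arms in mean change. Let the baseline gap be d × SD.
- Expected carry-over to 12 weeks: ρ × d × SD.
- Shift in the difference in change: ρ × d × SD − d × SD = −(1 − ρ) × d × SD.

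For d = 0.5 and SD = 3.18, in absolute size:

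| ρ | 0.5 × 3.18 × (1 − ρ) | Share of 4 points |
|---|---|---|
| 0.3 | 1.11 | 28% |
| 0.5 | 0.80 | 20% |
| 0.7 | 0.48 | 12% |

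The shift is proportional to the SD: at ρ = 0.5 it would be 1.0 point for SD 4 and 1.25 points for SD 5. An arm that starts worse appears to improve more. A raw comparison of final scores is shifted the opposite way, by ρ × d × SD, which is also 0.80 at ρ = 0.5.

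**5. What adjustment gains.** Per-arm variance terms, relative to SD²:
- Change score: 2(1 − ρ).
- ANCOVA: 1 − ρ².
- Ratio, ANCOVA to change score: (1 + ρ)/2 = 0.65, 0.75 and 0.85 for ρ = 0.3, 0.5 and 0.7.

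The variance falls by 35%, 25% and 15%. ANCOVA also removes the shift in step 4, because it subtracts the expected carry-over ρ × d × SD.

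**6. Arm sizes, only if the list is unrestricted.** With Binomial(22, 0.5), P(11:11) = 16.8% and P(8:14 or worse) = 28.6%. If 11:11 gives 80% power, 9:13 gives 78.7%, 8:14 gives 76.9%, 7:15 gives 74.2% and 6:16 gives 70.4%. Averaged over all splits, power is 78.0%, a loss of about 2 points. Blocking hardly affects step 2: the chance of a 0.5 SD gap is 25.3% with an unrestricted list and 24.1% at a fixed 11:11.

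**The case against.** A reader might infer that allocation is by simple randomisation, so that arm sizes are left to chance. The article does not support this. A blocked list, or one fixed at 11:11, is also a computer list of random numbers, and a condensed article commonly leaves block details to the full protocol. The arm-size figures are therefore conditional, and even then the average power loss is small. This part of the objection stands.

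A reader might also infer that this method of randomisation makes homogeneous groups impossible. That goes too far. Balance is not assured, but it is possible, and the cause is the sample of 22 rather than the list, since forcing equal arms barely changes covariate balance.

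The Ethic section gives ethics, not homogeneity, as its reason for allowing other treatment. Its homogeneity statement covers concomitant treatment, not baseline severity, and it already promises monitoring. All of this is correct. The baseline ICIQ-SF point therefore concerns the model in Statistical analysis and does not test the Ethic statement.

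Finally, baseline ICIQ-SF is already in the mixed model as an outcome, and chance imbalance does not invalidate a randomised test, because it is reflected in the standard error. The second half stands. The first does not settle the matter: with a free group effect at baseline, the interaction is a difference in change, which retains the shift shown in step 4.

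**Conclusion.** The concern holds in a limited form. The Ethic section attributes to randomisation and sample size a property that 22 women do not assure, and that randomisation cannot give at all for treatment begun after allocation. The model in Statistical analysis leaves a chance baseline gap in the effect estimate. A 0.5 SD gap, which arises in about 1 trial in 4 at 11:11, moves the estimate by about 0.8 points (0.5 to 1.1), or 12% to 28% of the 4-point target. Adjusting for baseline removes that shift and cuts the variance by 15% to 35% relative to change scores.

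These sizes rest on an SD of 3.18 solved from the stated sample size, equal SDs at both times, correlations of 0.3 to 0.7, and for the treatment count an assumed 20% use. The finding does not make the randomised comparison invalid, and it does not show the randomisation procedure to be wrong. It concerns how precisely and how safely the single estimate can be read.

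**What to change.** 1. **Statistical analysis.** Define the primary estimate as the 12-week between-group difference in ICIQ-SF adjusted for baseline ICIQ-SF, by ANCOVA or by a mixed model that constrains the two arms to a common baseline mean.
2. **Ethic.** Delete the expectation of homogeneous groups. State instead that concomitant incontinence treatment up to 12 weeks will be recorded and reported by arm.
3. **Randomization and blinding process (secondary and conditional).** State the allocation ratio and any restriction. If the list is unrestricted, have the independent researcher generate it in permuted blocks of varying size that are concealed from recruiters. This steadies arm sizes but does not itself improve covariate balance.

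The cost is a few sentences. ICIQ-SF is already collected at baseline, monitoring of concomitant treatment is already promised, an independent list generator and sealed envelopes are already planned, and Trials status says recruitment has not begun. The one drawback of blocking is that the last allocation in a block may be guessed, which varying and concealing the block sizes limits.

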### Intervention

Women randomized to Group 1 will receive counseling from the hospital staff. They will attend 3 meetings (once a month), where a multi-professional team from the bariatric surgery outpatient clinic will address different topics related to nutrition including advice on the quality of food, mindful eating, identification of signs of hunger and satiety, and emotional triggers that lead to emotional eating. In addition, each participant will undergo individual nutritional assistance to assess food consumption, anthropometric measures, and body composition and will receive more specific guidelines on nutrition and an individualized low-calorie diet and monitoring. Outpatient care will last 12 weeks and women in this group will not receive instructions and a supervised PFMT protocol, however for ethical reasons, after the data collection is finished women belonging to this group will be invited to receive six supervised sessions of PFMT and will receive the same booklet of exercises on PFMT delivered to group II.

The participants randomized to group II will also receive the same counseling related to nutrition and also an individualized low-calorie diet given by the hospital staff; additionally, they will participate in six face-to-face physiotherapy sessions supervised by a physiotherapist in groups of a maximum of 10 participants, for 12 weeks in interspersed weeks.

In the weeks when there is no face-to-face supervised session, the same physiotherapist will encourage home PFMT by phone, calling each participant of Group II only. An intensive PFMT will be encouraged by the physiotherapist. The PFMT protocol will consist of 4 sets of ten maximum perceived voluntary contractions sustained for 6 s with a 6-s resting period between the contractions. At the end of a series of 10 contractions, five rapid contractions of the PFM will be performed. Two minutes interval will be given between each set performed.

The sets will be performed only in two positions at the face-to-face supervised sessions at the hospital: sitting and standing (2 sitting sets + 2 standing sets). The participants of this group will be instructed to perform PFMT at home at least three times a week, except on the days of supervised training. They will be instructed to follow the booklet given to them in the first meeting, in addition to the fortnightly adherence diary to the exercises to be filled weekly. Participants will also be instructed on how to perform the “the knack” maneuver, which consists of repeatedly contracting their PFM before any increase in intra-abdominal pressure during daily activities [14]. Women will also be instructed to repeatedly contract their PFM when they feel urgency. Women will fill a diary about their adherence to PFMT, and there will be a place where they are asked about any side effects or bother related to the intervention. At the last assessment, they are asked about again about any unintended effects related to the trial intervention. The type and number of unintended effects will be fully reported as an important result of the trial. Although adverse effects of these type of intervention is not very common or severe, all the participant is assured they can discontinue their participation at any time for any reason, including any adverse effects (Table 1). Table 1 presents detailed information about the protocol of intervention.

**Table 1 Tab1:** Stages of the study and information about the 12 weeks training

	Recruitment	
	1^st^ Physical therapy evaluation	
	Randomization	
Week 1	Face-to-face session	4 sets (2 sitting sets + 2 standing sets) of ten maximum perceived voluntary contractions sustained for 6 s with a 6-s resting period between the contractions. At the end of a series of 10 contractions, five rapid contractions of the PFM will be performed. Two minutes interval will be given between each set performed in each position
Week 2	Face-to-face session	4 sets (2 sitting sets + 2 standing sets) of ten maximum perceived voluntary contractions sustained for 6 s with a 6-s resting period between the contractions. At the end of a series of 10 contractions, five rapid contractions of the PFM will be performed. Two minutes interval will be given between each set performed in each position
Week 3	Face-to-face session	4 sets (2 sitting sets + 2 standing sets) of ten maximum perceived voluntary contractions sustained for 6 s with a 6-s resting period between the contractions. At the end of a series of 10 contractions, five rapid contractions of the PFM will be performed. Two minutes interval will be given between each set performed in each position
Week 4	Face-to-face session	4 sets (2 sitting sets + 2 standing sets) of ten maximum perceived voluntary contractions sustained for 6 s with a 6-s resting period between the contractions. At the end of a series of 10 contractions, five rapid contractions of the PFM will be performed. Two minutes interval will be given between each set performed in each position
Week 5	Face-to-face session	4 sets (2 sitting sets + 2 standing sets) of ten maximum perceived voluntary contractions sustained for 6 s with a 6-s resting period between the contractions. At the end of a series of 10 contractions, five rapid contractions of the PFM will be performed. Two minutes interval will be given between each set performed in each position
Week 6	Face-to-face session	4 sets (2 sitting sets + 2 standing sets) of ten maximum perceived voluntary contractions sustained for 6 s with a 6-s resting period between the contractions. At the end of a series of 10 contractions, five rapid contractions of the PFM will be performed. Two minutes interval will be given between each set performed in each position
Week 7	Face-to-face session	4 sets (2 sitting sets + 2 standing sets) of ten maximum perceived voluntary contractions sustained for 6 s with a 6-s resting period between the contractions. At the end of a series of 10 contractions, five rapid contractions of the PFM will be performed. Two minutes interval will be given between each set performed in each position
Week 8	Face-to-face session	4 sets (2 sitting sets + 2 standing sets) of ten maximum perceived voluntary contractions sustained for 6 s with a 6-s resting period between the contractions. At the end of a series of 10 contractions, five rapid contractions of the PFM will be performed. Two minutes interval will be given between each set performed in each position
Week 9	Face-to-face session	4 sets (2 sitting sets + 2 standing sets) of ten maximum perceived voluntary contractions sustained for 6 s with a 6-s resting period between the contractions. At the end of a series of 10 contractions, five rapid contractions of the PFM will be performed. Two minutes interval will be given between each set performed in each position
Week 10	Face-to-face session	4 sets (2 sitting sets + 2 standing sets) of ten maximum perceived voluntary contractions sustained for 6 s with a 6-s resting period between the contractions. At the end of a series of 10 contractions, five rapid contractions of the PFM will be performed. Two minutes interval will be given between each set performed in each position
Week 11	Face-to-face session	4 sets (2 sitting sets + 2 standing sets) of ten maximum perceived voluntary contractions sustained for 6 s with a 6-s resting period between the contractions. At the end of a series of 10 contractions, five rapid contractions of the PFM will be performed. Two minutes interval will be given between each set performed in each position
Week 12	Face-to-face session	4 sets (2 sitting sets + 2 standing sets) of ten maximum perceived voluntary contractions sustained for 6 s with a 6-s resting period between the contractions. At the end of a series of 10 contractions, five rapid contractions of the PFM will be performed. Two minutes interval will be given between each set performed in each position
	2^st^ Physical therapy evaluation (Group I and II)	
	Diary about the adherence to PFMT	Women will fill a diary about their adherence to PFMT, and there will be a place where they are asked about any side effects or bother related to the intervention. At the last assessment, they are asked about again about any unintended effects related to the trial intervention. The type and number of unintended effects will be fully reported as an important result of the trial. Although adverse effects of these type of intervention are not very common or severe, all the participant is assured they can discontinue their participation at any time for any reason, including any adverse effects

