#### Other outcome measures

The adherence to home PFMT sessions will be monitored by the physiotherapist from a diary where women will register their adherence to home training. This diary will be attached to the leaflet that will be given to women in the first session. The diary will be collected by the physiotherapist every fortnight.

The PFM function will be assessed using vaginal palpation by a trained physiotherapist who will not be involved with the intervention and will not be aware of women’s allocation in the groups. Before the start of the palpation exam, the woman will receive detailed information about the anatomy, function, and dysfunction of the PFM and how to contract them correctly. The evaluation will be carried out with the participant in the supine position with the hip and knee semi-flexed. The participant will be asked to pull their PFM in and up as hard as possible, and then she will be instructed to relax them completely. Contraction of PFM will be classified as absent or present. The ability to contract the PFM will be considered present when there is occlusion and/or occlusion and elevation of the PFM towards the pubic symphysis and absent when there is no perceived internal movement. Additionally, muscle contraction will be graded according to the Modified Oxford Grading Scale (MOGS) [15, 16]. Contractions of muscles such as gluteus, adductor, and abdominal will be discouraged by the examiner.

Self-perception of women’s PFM contraction will be assessed at the time of the physical evaluation when the examiner will ask the participant if she feels she is able to contract her PFM and she will be asked to estimate the intensity of her PFM according to the MOGS that will be presented to her [17].

Participants’ subjective satisfaction with the treatment will be measured by the visual analog scale (VAS), which is an estimate on a numerical scale where 0 represents no satisfaction at all and 10 means the maximum possible satisfaction with the treatment.

In relation to satisfaction with the interventions, participants will be asked to answer the following questions: “Are you satisfied with the treatment you received for UI?”, “Would you do this treatment again?”, “Would you recommend this treatment?”, “Would you pursue another treatment?”. The options of answers to these questions are yes or no.

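### Unintended effects are prompted repeatedly only through a diary that by context group II alone keeps, and it is unclear whether group I is ever asked, so total counts would not be comparable between arms

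*Protocol article*

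**What the plan says.** The Intervention section describes two sources for unintended effects.

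- **The diary.** "Women will fill a diary about their adherence to PFMT", and in it "there will be a place where they are asked about any side effects or bother related to the intervention". It is to be completed weekly and handed in fortnightly: the Intervention section lists it "in addition to the fortnightly adherence diary to the exercises to be filled weekly", and Other outcome measures adds: "The diary will be collected by the physiotherapist every fortnight".
- **A question at the last assessment.** The next sentence says that the women are asked again at that visit. It does not name a group.

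On reporting, the same paragraph states: "The type and number of unintended effects will be fully reported as an important result of the trial".

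The diary is introduced in the part of the Intervention section that describes group II ("The participants of this group will be instructed to perform PFMT at home at least three times a week"). Other outcome measures ties it to the PFMT material: "This diary will be attached to the leaflet that will be given to women in the first session". Of group I, the Intervention section says that "women in this group will not receive instructions and a supervised PFMT protocol"; these women are offered the PFMT sessions and booklet only once data collection is over. Both groups are to receive an individualized low-calorie diet, and under Data collection both are assessed at baseline and after 12 weeks.

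**The concern.** Counts of unintended effects depend on how often and how directly people are asked. Here one arm has a standing written prompt for 12 weeks and regular contact with the physiotherapist who collects the diary. The other arm has, at best, one question at the end covering the whole period.

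In a two-arm randomized trial, a table of type and number by arm will be read as a comparison even if no test is attached. A reader could then take a difference in asking for a difference in tolerability, at the expense of diet plus PFMT. If the question is meant to cover the whole treatment, diet-related effects could also be noted in group II and missed in group I, although both arms follow the diet.

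**Working it through.** The article gives no figure for unintended effects, so there is no plan figure to reproduce. The check has two parts: the passages side by side, then an illustration based on stated assumptions.

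**1. Who is asked, and when**

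| Source of reports | Group II | Group I |
|---|---|---|
| PFMT diary field, filled weekly, collected fortnightly (Intervention; Other outcome measures) | Yes | None described; no PFMT material until data collection ends |
| Phone calls in weeks without a supervised session (Intervention) | Yes, an extra occasion to mention problems | No, calls are reserved for group II |
| Question at the last assessment (Intervention; Table 1) | Yes | Unclear |

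That only group II keeps the diary is an inference. Tables 1 and 2 list the diary without naming a group. It is a strong inference, because a record of adherence to PFMT has no use in an arm without PFMT.

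The last-assessment question can be read two ways. Asking women *again* presupposes that they were asked before, which holds only for diary keepers, and Table 1 puts the sentence in the diary row. On the other side, that row comes directly after the evaluation row labelled for both groups, and Data collection says that all assessments are done in both groups. The text does not settle it.

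**2. What unequal asking could do to the counts**

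Assumptions, none of them from the document:
- the true risk p is the same in both arms;
- the end-of-study question detects an affected woman with probability s, in both arms;
- the diary detects her with probability d, independently, in group II only.

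Expected reported risks:
- group I: p × s
- group II: p × [1 − (1 − s)(1 − d)]

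Apparent ratio, II to I: [1 − (1 − s)(1 − d)] / s. The true risk cancels.

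| s | d | Calculation | Apparent ratio |
|---|---|---|---|
| 0.9 | 0.9 | (1 − 0.1 × 0.1) / 0.9 = 0.99 / 0.9 | 1.10 |
| 0.7 | 0.5 | (1 − 0.3 × 0.5) / 0.7 = 0.85 / 0.7 | 1.21 |
| 0.5 | 0.8 | (1 − 0.5 × 0.2) / 0.5 = 0.90 / 0.5 | 1.80 |
| 0.3 | 0.9 | (1 − 0.7 × 0.1) / 0.3 = 0.93 / 0.3 | 3.10 |

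The ratio equals 1 + d(1 − s)/s, so it exceeds 1 whenever the diary detects anything (d > 0) and the final question is imperfect (s < 1). If the comparison uses only the final question, put to both arms, the ratio is s / s = 1.00. If group I is never asked, no ratio can be formed.

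In women rather than ratios: take p = 0.20, s = 0.5, d = 0.8, and 11 per arm. The 11 assumes that the 22 participants under Sample size calculation are the total and are split equally; the section states neither.
- group II: 0.20 × 0.90 = 0.18, and 0.18 × 11 = 1.98 women
- group I: 0.20 × 0.50 = 0.10, and 0.10 × 11 = 1.10 women

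The gap is about one woman, and it shrinks in proportion if effects are rarer. Group II's reported 18% is still below the assumed true 20%. What is distorted is the contrast between the arms, not group II's own rate upwards.

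**The case against.** The strongest case against has four parts.

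- **No comparison is planned.** The article promises only a description of type and number. Unintended effects are not in the Statistical analysis section, among the listed outcomes or in Table 2. This stands: the bias arises only if someone sets the arms' totals side by side.
- **The diary may simply monitor PFMT.** Both prompts ask about effects related to the intervention, straight after the exercises are described. On that reading, an empty entry for group I is correct. The reading is fair, but the reporting promise carries no such limit, so the protocol should say so if it is meant.
- **The common source may already exist.** If group I is asked at the last assessment, a fair comparison is available without any new question. This also stands, but the wording does not secure it.
- **An article leaves details to the full protocol.** Forms, question wording and recall windows commonly sit there. Their absence is not the point here; the collection route that the article does describe differs by arm.

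A reader might go further and infer that any comparison of harms between arms is biased against PFMT, or that harm in group II will be overstated. The document supports neither. A comparison restricted to one question asked of both arms would be balanced, and more prompting makes group II's count more complete rather than inflated. Nor does any passage say that the PFMT diary is meant to collect diet-related effects.

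**Conclusion.** The point holds in limited form. The only repeated prompt for unintended effects sits in a diary that, by context, only group II keeps; nothing comparable is described for group I; and it is open whether group I is asked at the end. A comparison of total counts would mix treatment effects with unequal ascertainment, in the direction that makes group II look relatively worse.

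The direction follows from the design, provided that the diary picks up some effects that the final question misses. The size does not: the ratios of 1.10 to 3.10 rest wholly on assumed detection probabilities, and with 11 women per arm the illustrated gap is about one woman. The primary outcome and its analysis are untouched. This is a cheap improvement to the collection and reporting of unintended effects, not a flaw in the trial's main question.

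**What to change.** In the Intervention section, and in the matching row of Table 1:

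1. State that both groups are asked the same question about unintended effects of any part of the treatment received, with the same recall window, at the 12-week assessment.
2. Ask it after palpation and the ICIQ-SF are complete, so that an answer mentioning exercises cannot unmask the assessor before those measurements.
3. Base any between-arm statement on this common question only, and report diary entries separately as a description of group II.

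The cost is one question at a visit that both groups already attend, plus one reporting sentence. Trials status says that recruitment has not begun, so the change can be made before any data exist. The downside is that counts from the common question will be less complete than the diary; reporting the diary alongside, labelled as group II only, keeps that information.
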